### CAS Diagnosis in English-Speaking Children

The gold standard for making a CAS diagnosis primarily relies on perceptual judgments of CAS experts. However, very recently, a pilot study reported only moderate agreement among 4 expert listeners [10]. Along with perceptual judgment, the maximum performance tasks (MPT) [11] and Syllable Repetition Task (SRT) [12] have been reported to provide valuable relevant information about segmental sequencing skills in children with CAS. Both MPT and SRT assess deficits in speech processing. The MPT aims to assess motor involvement in children with speech problems [11]. Specifically, the maximum repetition rate for trisyllabic stimuli (MRRtri) and maximum fricative duration (MFD) in MPT assess underlying deficits in the motor planning and programming of speech [13], while the maximum repetition rate for monosyllabic stimuli and maximum phonation duration assess deficits in speech motor execution. The SRT targets encoding, memory, and transcoding processes, which refer to mapping, prearticulatory or phonological planning, and transformation of the phonological plan into a motor plan, respectively [14]. Although the terminology is not identical, both the MPT and SRT address the same underlying deficits of CAS, speech motor planning and programming skills. Research has shown that the MPT has high sensitivity and specificity (ranging from 89% to 100%) in making a CAS diagnosis [11], whereas a cutoff transcoding score of 80 on the SRT is able to differentiate children with CAS from children with concomitant speech delay and language impairment (LI) [15].

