### The Goal of the Proposed Study

This study aims the following:

To show that the MPT and SRT can contribute to the diagnosis of CAS in Cantonese-speaking children.To document differences in pitch-variation skills in Cantonese-speaking children with versus without CAS.To prove that TSTs are effective in diagnosing CAS in Cantonese-speaking children.

We hypothesized the following:

The MPT and SRT would differentiate Cantonese-speaking children with CAS from those without CAS.Cantonese-speaking children with CAS would have significantly poorer pitch-variation skills than the control groups.TSTs would differentiate Cantonese-speaking children with CAS from those without CAS.

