### Study Design

This is a comparative accuracy study that will compare the diagnostic accuracy of the MPT, SRT, and TST in children with and without CAS.

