### Participants

A total of 25 children with CAS will be recruited for the study. The inclusion criteria are as follows: (1) age between 3 years and 6 years 11 months, (2) diagnosed with or suspected of having CAS by a qualified speech-language pathologist, (3) no hearing impairment or structural abnormality that affects speech production, and (4) Cantonese as the main language for daily communication. The same number of age- and gender-matched children will be recruited for each of the following 3 control groups: non-CAS SSDs only, non-CAS SSDs co-occurring with S&LI, and TD. The non-CAS SSD group will be recruited because it will allow a direct comparison between children with and without CAS. Research has shown that LI is usually present in children with CAS [5]; therefore, an S&LI group will be included to compare the performance of children with and without CAS, while controlling for language skills. A total of 100 participants will be recruited. Originally, a sample size of 172 participants (ie, 43 for each group) was estimated from the effect size of tone accuracy in a pilot study [20] via power analysis. An actual power of 0.954 could be achieved from 172 participants with an error probability of 0.05 (*F*_168_=2.658). There should be sufficient children with CAS in this population. However, taking into consideration the time and effort needed to screen and find suitable participants with and without CAS, SSD, and S&LI, it will be very challenging to recruit 172 participants within 2 years (the proposed study period). In addition, many reported studies [22,23] have only recruited 20 to 30 children with CAS for the investigations of assessment and diagnostic accuracy. Therefore, the total sample size was reduced to 100 participants.

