### Statistical Methods

For the statistical analysis, linear mixed-effects models will be used. Our models will include group (CAS vs SSD vs S&LI vs TD) as a fixed effect and participants and items as random effects.

The sensitivity and specificity of the MPT, SRT, and TST in making a diagnosis of CAS in Cantonese-speaking children will be determined using the receiver operating characteristics curve [40]. The new cutoff scores of the MPT and SRT to diagnose CAS in Cantonese-speaking children will be compared with the existing cutoff scores recommended for English-speaking children. The cutoff scores for the TST will also be determined from the receiver operating characteristics curve.

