## Results

Data collection started in January 2022 but was soon disrupted by the fifth wave of the COVID-19 pandemic in Hong Kong. As of August 2022, the project has recruited 4 children in the CAS group, 21 children in the non-CAS SSD group, 4 children in the S&LI group, and 53 children in the TD group. Data collection is ongoing and will continue until October 2023.

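### The ROC negatives are not restricted to children with speech disorders; pooling typically developing children, the natural reading, would raise specificity and shift the cutoffs

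*Protocol article*

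**What the plan says.** All references are to the protocol article.

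- **Study Design:** the study "will compare the diagnostic accuracy of the MPT, SRT, and TST in children with and without CAS".
- **The Goal of the Proposed Study:** the two diagnostic hypotheses are "The MPT and SRT would differentiate Cantonese-speaking children with CAS from those without CAS" and "TSTs would differentiate Cantonese-speaking children with CAS from those without CAS". Neither limits the comparison group to children with a speech disorder.
- **Participants:** 25 children with CAS are planned, and "The same number of age- and gender-matched children will be recruited for each of the following 3 control groups": speech sound disorder (SSD) only, SSD with language impairment (S&LI), and TD. The SSD group is justified as the direct comparator for CAS, and the S&LI group as a way to control for language skills.
- **Statistical Methods:** "The sensitivity and specificity of the MPT, SRT, and TST in making a diagnosis of CAS in Cantonese-speaking children will be determined using" the ROC curve. New MPT and SRT cutoffs are to be compared with the English ones, and TST cutoffs come from the same method. The negatives are not named, and no accuracy estimate against SSD or S&LI alone is stated. The mixed models keep four groups apart, but they compare means.
- **Results:** by August 2022 there were 4 children with CAS, 21 with SSD, "4 children in the S&LI group, and 53 children in the TD group".
- **CAS Diagnosis in English-Speaking Children:** an SRT transcoding cutoff of 80 "is able to differentiate children with CAS from children with concomitant speech delay and language impairment (LI").

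**The concern.** The article wants these tests for differential diagnosis. CAS Diagnosis in Cantonese-Speaking Children speaks of misdiagnosis and underdiagnosis and their effect on how treatment is allocated, and the Dissemination Plan returns to clinicians' lack of confidence in differential diagnosis. The hard decision is between CAS and another speech disorder. A child with typical speech is probably an easy negative, and each one added to the pool pulls specificity upward without telling the clinician anything about that decision.

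Three results are at stake:

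1. The reported specificity would depend partly on how many TD children were enrolled.
2. The cutoff chosen on the pooled curve would move, and that cutoff is what clinicians would use.
3. The planned comparison with the English SRT transcoding cutoff would mix a difference of language with a difference in the kind of control. The article states the comparator only for that one cutoff, so this third point does not extend to the MPT or the other SRT scores.

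**Working it through.** **The plan's own figures.** The article gives no expected specificity, AUC or precision target. Its only power calculation (172 participants, power 0.954) concerns group means. The critical value F(3, 168) at 0.05 reproduces as 2.658, but the effect size behind the power is not stated, and the calculation does not bear on accuracy.

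**Step 1. Share of TD among controls.**
- Planned: 25/75 = 33.3%.
- Recruited by August 2022: 53/(21 + 4 + 53) = 53/78 = 67.9%.
- If SSD and S&LI reach 25 each and all 53 TD children are analysed: 53/103 = 51.5%.

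**Step 2. Effect of pooling at a fixed cutoff.** With TD share w, specificity S_D against disordered controls and S_T against TD:

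S_pooled = (1 − w)·S_D + w·S_T = S_D + w·(S_T − S_D).

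The excess over S_D is one third of the gap at the planned mix, about half at 53/103 and about two thirds at 53/78. This needs only S_T > S_D.

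**Step 3. Illustrative size.** The inputs are assumptions. The values 1.37 and 1.98 are the ends of the pilot range for tone accuracy (Previous Pilot Studies). The article does not split that range by control group, so giving the low end to disordered controls and the high end to TD is a choice made here. The value 0.74 is not in the article; the first pilot, against two children with SSD, reported 0.68. Scores are taken as normal with equal variance.

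At 80% sensitivity the cutoff lies z = 0.842 SD above the CAS mean, so specificity = Φ(d − 0.842), and AUC = Φ(d/√2).

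- d = 0.74: Φ(−0.102) = 46.0%; AUC 0.70
- d = 1.37: Φ(0.528) = 70.1%; AUC 0.83
- d = 1.98: Φ(1.138) = 87.3%; AUC 0.92

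| Negatives | Specificity, d = 0.74 | Specificity, d = 1.37 |
|---|---|---|
| SSD + S&LI only | 46.0% | 70.1% |
| Pooled, 50 disordered + 25 TD | 59.7% | 75.8% |
| Pooled, 50 disordered + 53 TD | 67.2% | 78.9% |

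First pooled row: (2 × 46.0 + 87.3)/3 = 59.7 (one decimal from unrounded values), and (2 × 70.1 + 87.3)/3 = 75.8. Pooled AUC at the planned mix is 0.77 to 0.86, against 0.70 to 0.83 for disordered controls alone.

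**Step 4. Shift of the cutoff.** Take an assumed separation of 1 SD from disordered controls and 2 SD from TD, with the cutoff that maximises the Youden index:

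| Cutoff set on | Sensitivity | Pooled specificity | Specificity against disordered |
|---|---|---|---|
| Disordered only | 69% | not applicable | 69% |
| Planned pool (w = 1/3) | 76% | 71% | 62% |
| August 2022 mix (w = 53/78) | 81% | 77% | 55% |

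As TD children are added, the headline specificity rises while the specificity in disordered children falls.

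**The case against.** **The negatives are never named.** Statistical Methods does not say that TD children are pooled. Participants uses the with-and-without-CAS contrast when explaining the SSD and S&LI groups, so the authors may have disordered controls in mind. This stands: a reader might infer that the plan defines specificity on a pool including TD and that specificity is therefore inflated, but the text supports only that it would be inflated if they are pooled. Pooling remains the natural reading of the hypotheses and Study Design.

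**A condensed article may leave the ROC sets to a fuller plan.** This is fair for detail, and the separate groups in the mixed model show that group identity is kept. But the contrast itself is stated here, in the hypotheses and the design, and it answers the article's own clinical question less well than a comparison with disordered controls.

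**The 68% is a snapshot.** This stands. Recruitment runs to October 2023, the design is 33%, and nothing says that the 28 TD children beyond the planned 25 will enter the ROC analysis. A reader should not take 68% as the analysis mix.

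**The size rests on thin inputs.** This stands too. The pilot range comes from four children with CAS, covers tone accuracy only, and says nothing about the MPT or SRT. At d = 1.37 and the planned mix, the difference is modest (70% to 76%).

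**Conclusion.** The point holds in conditional form. The accuracy question is worded as CAS versus no CAS, the ROC negatives are unrestricted, and one third of planned controls are typically developing. If TD children are pooled and are easier to classify, specificity is overstated for differential diagnosis by one third of the gap at the planned mix, and by more if surplus TD children are analysed. Under the stated assumptions that is about 14 points at d = 0.74 (46% to 60%) and 6 points at d = 1.37 (70% to 76%). The direction is firm on that condition; the size is illustrative.

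Two stronger readings are not supported. A reader might say that the pooled curve merely separates CAS from healthy children, but at the planned mix two thirds of the negatives have a speech disorder. A reader might also infer that suspected cases not confirmed by both experts are excluded. Initial Assessment says only that CAS is confirmed by consensus. The place of the unconfirmed children in the analysis is not stated, and they could enter the SSD or S&LI group.

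**What to change.** State that the primary ROC curves, cutoffs, sensitivity and specificity for the MPT, SRT and TST compare CAS with SSD plus S&LI. Report CAS versus TD separately, and do not pool TD into the headline specificity. Make the comparison with the English SRT transcoding cutoff on the disordered-control analysis.

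As a secondary point, state where suspected-CAS children go when the two experts do not both confirm CAS. Keeping them among the non-CAS disordered negatives, with a sensitivity analysis that excludes them, would retain what are likely the hardest negatives.

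The cost is analysis wording, with no new recruitment. Planned negatives fall from 75 to 50. At an assumed specificity of 80%, the approximate 95% half-width grows from 1.96·√(0.16/75) = 9.1 points to 1.96·√(0.16/50) = 11.1 points. The reported figure will probably be less favourable.

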Scores	MPD^a^: mean duration of the longest prolongation of [a] and [mama] MFD^b^: mean duration of the longest prolongation of [s], [f], and [z] MRRmono^c^ score: mean repetition rate for the fastest repetition of each [pa], [ta], and [ka] MRRtri^d^ score: number of syllables produced per second in the child’s fastest repetition of [pʌtʌkʌ] Sequence score: 1 for correct sequence and 0 for unsuccessful production Attempt score: number of attempts required to produce the correct sequence	Competency: PCC^e^ of 18 items Encoding: percentage of consonants within-manner class substitution errors (excluding voicing errors) Memory: ratio of PCC for 3-syllable items to PCC for 2-syllable items Transcoding: percentage of items that are produced with ≥1 additions
Interpretation of the scores	MFD and MRRtri scores are used to obtain a dyspraxia score (0, 1, or 2), while MPD and MRRmono scores are used to obtain a dysarthria score (0, 1, or 2)	Interpretation of these 4 scores is made based on the z-scores from the means and SDs reported in the study by Lohmeier and Shriberg [36]
Criteria of CAS^f^ diagnosis	A dyspraxia score of 2 indicates the presence of CAS; it is obtained when MRRtri ≤3.4 or Sequence=0 or Dyspraxia score is not 0 or 1	Cutoff scores for CAS diagnosis [37]: Competency score=65 Encoding score=46.9 Memory score=67.5 Transcoding score=80

^a^MPD: maximum phonation duration.

^b^MFD: maximum fricative duration.

^c^MRRmono: maximum repetition rate for monosyllabic stimuli.

^d^MRRtri: maximum repetition rate for trisyllabic stimuli.

^e^PCC: percentage of consonants correct.

^f^CAS: childhood apraxia of speech.

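### Cutoffs and their sensitivity and specificity come from the same children with no validation named, so reported accuracy, chiefly sensitivity, would be optimistic

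*Protocol article*

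**What the plan says.** Statistical Methods states that the sensitivity and specificity of all three tests for diagnosing CAS will be obtained from the ROC curve. It then says of the two existing tests: "The new cutoff scores of the MPT and SRT to diagnose CAS in Cantonese-speaking children will be compared with the existing cutoff scores" recommended for English speakers. For the new test it says: "The cutoff scores for the TST will also be determined from the receiver operating characteristics curve".

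The sample is described in Participants: "A total of 25 children with CAS will be recruited for the study", "The same number of age- and gender-matched children will be recruited for each of the following 3 control groups", and "A total of 100 participants will be recruited". No second sample is described.

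The English SRT cutoffs are given in Table 1: "Competency score=65 Encoding score=46.9 Memory score=67.5 Transcoding score=80". The MPT rule there is a dyspraxia score of 2 on a scale of 0, 1 or 2, and that score depends in part on a threshold of 3.4 for the trisyllabic repetition rate.

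The article does not state the rule for picking a point on the ROC curve, or whether new and English cutoffs are to be compared as values or on their sensitivity and specificity.

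**The concern.** A ROC curve shows sensitivity and specificity at every possible cutoff, and no cutoff has yet been chosen. Once one cutoff is picked because it does well in these children, its sensitivity and specificity in the same children are partly a record of chance. With 25 children on the sensitivity side, the chance component is not negligible.

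The English cutoffs were fixed before these data were seen and carry no such gain. Set side by side on accuracy in this sample, one cutoff has been fitted to the data and the other has not.

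Diagnostic accuracy is the declared purpose of the study, and Strengths and Limitations presents the expected result as fast, accurate methods for clinicians. Uncorrected figures would promise more than new children will deliver.

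**Working it through.** **The plan's own figure.** The only numerical target is the power calculation for the four-group comparison: 172 children, power 0.954, critical F 2.658. The critical value is reproduced (F at 0.95 with 3 and 168 degrees of freedom = 2.658). The power cannot be, because the ANOVA effect size is not given. Neither figure concerns sensitivity, specificity or cutoffs.

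**Inputs from the article.** 25 CAS; 3 × 25 = 75 non-CAS. Pilot effect sizes for tone accuracy: d = 0.68 (first TST version), and d = 1.37 to 1.98 (later pilot).

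**Assumptions, not in the article.** Normal scores with equal variance; the three control groups pooled; cutoff chosen to maximise the Youden index J = sensitivity + specificity − 1.

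**Best achievable accuracy.** The true optimum lies midway between the two means, giving J = 2Φ(d/2) − 1 = 0.266, 0.507 and 0.678 for d = 0.68, 1.37 and 1.98.

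**Simulation, 10,000 samples of 25 versus 75 per effect size.** Apparent means read in the same sample; true means the performance of that chosen cutoff in new children.

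| d | Sensitivity, apparent / true | Specificity, apparent / true | Excess in J |
|---|---|---|---|
| 0.68 | 0.706 / 0.621 | 0.649 / 0.622 | 0.112 |
| 1.37 | 0.810 / 0.741 | 0.765 / 0.743 | 0.091 |
| 1.98 | 0.882 / 0.825 | 0.851 / 0.832 | 0.076 |

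By subtraction, sensitivity is overstated by 8.5, 6.9 and 5.7 points and specificity by 2.7, 2.2 and 1.9 points. Sensitivity suffers more because it rests on 25 children and specificity on 75.

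**Dependence on sample size.** In the same order of d, the excess in J is 0.138, 0.113 and 0.092 against a single control group of 25. At the originally estimated size (43 versus 3 × 43 = 129) it is 0.082, 0.066 and 0.056.

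**New versus fixed cutoff, if compared on same-sample J.** Suppose the existing cutoff is truly optimal. The new one then appears better by 0.089, 0.069 and 0.055, although it is truly worse by 0.023, 0.023 and 0.021. It scores strictly higher in 93% to 97% of samples and, by construction, never lower. At d = 1.37 with the existing cutoff misplaced by 0.5 SD, the apparent gain is 0.120 and the true gain 0.029; at 1 SD they are 0.243 and 0.153. The excess stays near 0.09 throughout (0.069 + 0.023 = 0.092; 0.120 − 0.029 = 0.091; 0.243 − 0.153 = 0.090).

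**Three-level score.** For two assumed distributions of a 0/1/2 score, the excess in J is only 0.034 and 0.015.

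**What a bootstrap recovers (600 samples, 100 resamples each).** Sensitivity, shown as apparent, corrected, true: 0.708, 0.653, 0.620 at d = 0.68; 0.806, 0.762, 0.735 at d = 1.37; 0.883, 0.847, 0.826 at d = 1.98. At d = 1.37 the share removed is (0.806 − 0.762)/(0.806 − 0.735) = 0.044/0.071 = 62%. Overall it is roughly half to two-thirds, so some optimism remains.

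**The case against.** The strongest reply is that Statistical Methods is two short paragraphs in a journal article. The cutoff rule, internal validation and confidence intervals are often left to a full analysis plan, and nothing printed excludes a correction. That stands as a reason not to treat silence as proof. It does not remove the point: the procedure that is stated, followed as written in the one sample described, gives biased figures on the study's main question.

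A second reply is that sampling error is larger than the optimism: 20 of 25 has an exact 95% interval of 0.59 to 0.93. That is true. However, an interval centred on an optimistic estimate does not correct it.

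Three stronger readings are tempting and are not supported.

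- A reader might infer that the comparison with the English cutoffs is set up so that the new ones win. The text speaks of comparing cutoff scores and may mean only their values. The one-sidedness arises only if accuracy is the metric, and no intent is shown.
- A reader might infer a search for the best of the four TST outcomes, four SRT scores or six MPT scores, with larger bias. The article announces no such selection. Its MPT rule for CAS uses the three-level dyspraxia score, which carries little optimism unless the underlying repetition-rate threshold is re-cut.
- A reader might object that a study meant to "compare the diagnostic accuracy of the MPT, SRT, and TST in children with and without CAS" describes no paired comparison of the tests. An article may leave that to the full plan, and because every child takes all three tests, a paired analysis remains possible.

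**Conclusion.** The point holds in a limited form. As described, the same 100 children supply both the cutoffs and the accuracy quoted at them. Under the stated assumptions and the pilot effect sizes, sensitivity would be overstated by about 6 to 8.5 points, specificity by about 2 to 3 points, and the Youden index by about 0.08 to 0.11. For a three-level MPT score the bias is minor. A same-sample accuracy comparison with the English cutoffs would favour the new cutoffs by roughly the same amount in the Youden index; a comparison of cutoff values alone would not raise this problem.

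It would be wrong to say that both measures rest on the 25 children with CAS. Specificity comes from the 75 without CAS, where the bias is small. The sizes depend on the Youden rule, normal scores, pooled controls and pilot effects that the article itself describes as coming from extremely small samples.

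**What to change.** 1. State the rule for choosing each cutoff, the score to which it applies, and whether new and English cutoffs are compared as values or on accuracy.
2. Repeat the whole cutoff search inside a bootstrap or repeated cross-validation, stratified by the four groups. Report optimism-corrected sensitivity and specificity with 95% confidence intervals.
3. Make any accuracy comparison between new and English cutoffs on the corrected values. Because some optimism survives the bootstrap, do not read a small remaining advantage as proof that the new cutoff is better.
4. Describe the new cutoffs as provisional until they are validated in a separate sample, and list this among the limitations.

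The cost of the first three items is a few lines of code, some wording and slightly lower reported accuracy. Recruitment, testing and data collection do not change. Validation in a separate sample is later work that this study need not carry out.
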